### Sample size calculations

Based on the volume of admissions at each study hospital, we plan to screen 7,548 potential subjects who are hospitalized on medical wards for greater than 24 hours during the enrollment period at the four sites. Based on chart review, we estimated smoking prevalence at each site (weighted average = 23%, range 17 to 32%), and determined that approximately 80% of identified smokers will be eligible to participate in the proposed trial. Assuming that 84% of eligible patients consent to participate (based on a recent VA smoking cessation study [47]), we would expect 1,000 subjects to enroll in the study (500 baseline, 500 intervention). Pooling the control group data from studies of general medical inpatients, we estimate a 12% quit rate at six-months (seven-day PPA). Thus, a study sample of 1,000 patients will have 83% power to detect a seven percentage-point difference between periods in six-month quit rates. This effect estimate is consistent with that observed in prior hospital intervention trials that employed a sustained relapse prevention component [16,20,21]. Based on chart reviews at two study sites, we estimate that 12 and 13% of inpatients during the baseline period will be referred for cessation counseling and will receive recommended pharmacotherapy, respectively. The projected study sample will have 81 and 83% power to detect a seven percentage-point difference in these process measures, respectively. These power calculations are based on a hierarchical linear model, with nurse treated as a random factor (and patient outcomes are clustered within nurse); intracluster correlation (ICC) was estimated to be 0.05 for assistance in quitting (which includes offering of pharmacotherapy and arranging follow-up), and 0.01 for abstinence, based on data from the AHRQ Smoking Cessation Guideline Evaluation Trial [77].

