### Study sites

We have selected four VA hospitals in the upper Midwest and Rocky Mountain region for this trial based on the following criteria: at least 150 general medical admissions monthly (to support recruitment targets), and support from nursing, pharmacy, and information technology (IT) leaders for this project. The variability in delivery of smoking cessation counseling across these study sites will enhance external validity, and may provide insight into the intervention's effectiveness under different baseline conditions (Table 1).

**Table 1 T1:** Description of VA study hospitals

	**Hospital A**	**Hospital B**	**Hospital C**	**Hospital D**
Patient characteristics				
Age, mean	62.9	65.1	62.7	60.4

Gender, % male	97	96	95	94

Race, % white	97	80	85	86

Income ($), mean	21,349	26,287	20,500	19,414

General medical wards				
Annual number of admissions, n	2,988	4,388	2,701	2,806

Total number of nursing staff	42	72	60	52

% Registered nurses (RN)*	67	68	73	58

Average daily census (across wards), n	29	62	33	42

Average nursing hours per patient day	6.2	7.13	8.31	7.34

Smoking cessation services**				
Responsible division	Mental health	Mental health	Mental health	Primary care

No. of consults per month	50	60	65	30

How often do new patients start program?	1/month	1/week	NS	1/week

No. of individual counseling sessions per typical course of therapy	3	NS	2	4

Program includes group counseling	Y	Y	N	Y

Can patients receive pharmacotherapy without enrollment in smoking cessation program?	Y	Y	N	Y

Any use of telemedicine to provide cessation therapy?	Y	N	Y	N

*Source: VHA Support Service Center.  (accessed 6/13/07). Nurse staffing was estimated from local data.

**Source: Office of the Assistant Deputy Undersecretary for Health for Policy and Planning. Veterans Health Administration. Smoking and Tobacco Use Cessation Report 2005.  (last accessed 1 December 2006).

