We will use an intent-to-treat approach in which patients are analyzed according to the period in which they were enrolled. In our analysis of three- and six-month cessation rates, those who are lost to follow-up will be considered failures (*i.e*., still smoking). Using this approach, however, some bias may be introduced on account of informative censoring (even if the pattern of missingness is evenly distributed across baseline and intervention periods). For this reason, we will also conduct analyses to examine the patterns of missingness, and will perform sensitivity analyses to compare intervention effects under a range of assumptions regarding the mechanism of missingness [85,86]. All tests will be two-sided and will use a p-value of 0.05 for statistical significance. To fit the hierarchical models, we will use SAS (PROC GLIMMIX).

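### The two process-measure powers (81% at a 12% baseline, 83% at a 13% baseline) are in an impossible order, and the stated recruitment rates give about 1,167 patients, not 1,000

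*Protocol article*

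**What the plan says.** All the figures are in the Sample size calculations section unless noted.

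- Enrolment: "we would expect 1,000 subjects to enroll in the study (500 baseline, 500 intervention"). The steps before it are 7,548 patients screened, 23% smokers (weighted average over sites), about 80% of smokers eligible and 84% of those consenting.
- Baseline process rates: "we estimate that 12 and 13% of inpatients during the baseline period will be referred for cessation counseling and will receive recommended pharmacotherapy, respectively".
- Process powers: "The projected study sample will have 81 and 83% power to detect a seven percentage-point difference in these process measures, respectively".
- Abstinence: "we estimate a 12% quit rate at six-months (seven-day PPA"), with 83% power for a seven-point difference.
- Clustering: the calculations use a hierarchical model "with nurse treated as a random factor (and patient outcomes are clustered within nurse"), with the ICC "estimated to be 0.05 for assistance in quitting (which includes offering of pharmacotherapy and arranging follow-up), and 0.01 for abstinence".
- Test, from Statistical analysis: "All tests will be two-sided and will use a p-value of 0.05 for statistical significance".

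The number of patients per nurse is not given. The nearest figure is the row "Total number of nursing staff" in Table 1 (Study sites), which sums to 42 + 72 + 60 + 52 = 226.

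**The concern.** The two process measures differ in one input only, the baseline rate. Below 50%, the binomial variance rises with the rate, so the same seven-point difference is harder to detect from 13% than from 12%. The text gives the higher power to the 13% measure, and the word fixing the order of each pair leaves no doubt which figure goes with which measure.

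The same paragraph sets out a multiplication whose stated result is not its product.

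Referral and pharmacotherapy are the primary process-of-care endpoints (Statistical analysis) and the subject of Hypothesis 1b. A reader who wants to know how well the trial is powered for them cannot rely on the printed pair. A reader checking feasibility cannot tell whether one of the recruitment rates is wrong or an allowance has been left out.

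**Working it through.** **Inputs from the protocol article.** 500 patients per period; two-sided alpha 0.05; difference 0.07; ICC 0.05 for both process measures; referral 12% to 19%; pharmacotherapy 13% to 20%.

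**Formula.** Power = Phi(0.07 / sqrt(DE x (p1q1 + p2q2) / 500) - 1.96), where DE is the design effect for clustering within nurse. DE depends on patients per nurse and the ICC, so it is the same for both process measures.

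**Variance terms.**
- Referral: 0.12 x 0.88 + 0.19 x 0.81 = 0.1056 + 0.1539 = 0.2595.
- Pharmacotherapy: 0.13 x 0.87 + 0.20 x 0.80 = 0.1131 + 0.1600 = 0.2731, about 5% larger.

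**No clustering (DE = 1).** Referral 0.07 / 0.02278 = 3.073, power 86.7%. Pharmacotherapy 0.07 / 0.02337 = 2.995, power 85.0%.

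**Trying to reproduce the stated pair.** DE is not stated, so I solve for it from one figure and read off the other.

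| Figure taken as right | DE needed | Referral | Pharmacotherapy |
|---|---|---|---|
| Stated in the article | not given | 81% | 83% |
| Referral 81% | 1.172 | 81.0% | 79.0% |
| Pharmacotherapy 83% | 1.056 | 84.8% | 83.0% |
| Figures exchanged (referral 83%) | 1.112 | 83.0% | 81.1% |

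No DE gives the stated order.

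**Sensitivity to the method.** Pooled variance, continuity correction, the arcsine form and one-sided testing all leave pharmacotherapy about 1 to 2 points below referral. The order also holds on the log-odds scale, which matters because the analysis is logistic. Without clustering, referral is 0.542 / sqrt(0.03193) = 3.04 and pharmacotherapy 0.515 / sqrt(0.03018) = 2.96.

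**Sensitivity to patients per nurse (assumption).** Taking Table 1's 226 nurses:
- Each period separately: 500 / 226 = 2.2 per nurse, DE = 1 + 1.21 x 0.05 = 1.061; referral 84.7%, pharmacotherapy 82.9%.
- Both periods together: 1,000 / 226 = 4.4 per nurse, DE = 1 + 3.42 x 0.05 = 1.171; referral 81.0%, pharmacotherapy 79.0%.

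So the 83% for pharmacotherapy fits one cluster size and the 81% for referral fits the other. They do not fit together.

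**Recruitment.** 7,548 x 0.23 = 1,736; x 0.80 = 1,389; x 0.84 = 1,167. If each rate is rounded to the nearest percent, the range is 7,548 x 0.225 x 0.795 x 0.835 = 1,127 to 7,548 x 0.235 x 0.805 x 0.845 = 1,207. Reaching 1,000 would need 1,000 / (7,548 x 0.80 x 0.84) = 19.7% prevalence, or 1,000 / (0.23 x 0.80 x 0.84) = about 6,470 screened. Equivalently, a further 1 - 1,000 / 1,167 = 14% is lost without mention.

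**The case against.** The best defence is that this is a typing slip. Exchange the two process figures and they agree with each other (83.0% and 81.1%). That stands as a possible explanation, perhaps the simplest.

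A reader might try to rule it out: referral at ICC 0.05 would then have the same 83% as abstinence at ICC 0.01, with the same 12% baseline and seven-point difference, although a lower ICC should give more power. The documents do not support that argument. Each site is its own control, so the same nurses may treat patients in both periods. Part of the nurse effect then cancels in the comparison, and a lower ICC need not raise power. Even with separate nurses in each period, a continuity-corrected calculation at about 1.8 patients per nurse gives 84.2% for abstinence, 83.0% for referral and 81.1% for pharmacotherapy, close to the exchanged figures.

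A reader might also infer that pharmacotherapy is powered below 80%. That follows only if 81% is right for referral. At 2.2 patients per nurse it is about 83%, as printed. For the same reason, replacement figures computed from Table 1's staffing should not be imposed: they assume that every listed nurse admits patients equally.

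On recruitment, the defence is that 1,000 is a rounded, cautious target. It is cautious, but the text presents it as the number expected from the stated rates, and rounding those rates does not reach it. Nor does loss to follow-up explain the gap: 1,000 is a count of patients enrolled, and patients lost later are analysed as smokers. A reader might think the enrolment figure determines how long recruitment must run. It does not, since Study design sets each period at six months.

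**Conclusion.** Both points hold, and both are modest.

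The printed process powers cannot stand as paired. This conclusion needs no assumption about patients per nurse, only the inputs that the article says the two measures share. The error is 2 to 4 points: with one figure kept, the other moves to about 79% (pharmacotherapy) or 85% (referral); with the figures exchanged, each moves by 2. Which case applies cannot be decided from the document.

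The expected enrolment of 1,000 is about 14% below what the stated rates give. The discrepancy is on the safe side, since the power calculations use the smaller number.

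Nothing here shows the trial to be underpowered. The 83% for abstinence is not shown to be overstated: at ICC 0.01 and 2.2 to 4.4 patients per nurse the stated inputs give about 83% to 86%, depending on the continuity correction.

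**What to change.** Recompute the abstinence, referral and pharmacotherapy powers by one method. State the number of patients per nurse and whether the same nurses contribute to both periods. Then restate the two process powers from that calculation, or exchange them if the source calculation shows a transposition.

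In the recruitment sentence, either give about 1,167 expected (about 583 per period) and keep 1,000 as the number used for power, or state the further allowance of about 14% that brings it to 1,000. If one of the rates is wrong, correct that rate instead.

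The cost is one rewritten paragraph. The sample size, the enrolment periods and the analysis stay as they are.

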### Statistical analysis

The primary clinical endpoint of this analysis is seven-day PPA at three and six months. The primary process of care endpoints are referral of patients to telephone counseling (or other outpatient cessation counseling) and prescription of recommended pharmacotherapy for smoking cessation. To evaluate the relationship between the intervention and these outcomes, we will use hierarchical logistic regression to adjust for differences in potentially confounding patient and nurse characteristics between the baseline and intervention period cohorts. In these analyses, each patient will be nested within his/her admitting nurse, who will have primary responsibility for providing brief cessation counseling. To compare how the two arms differ in time to first relapse after hospital discharge, we will use Cox proportional-hazards survival analysis methods with time to relapse as the outcome [83]; in this analysis, intra-nurse correlation will be accounted for by using the robust sandwich estimator [84].

To evaluate the hypothesis that staff nurses will have improved decisional balance scores and higher ratings of self-efficacy in providing cessation counseling as a result of the intervention, we will compare values of these measures obtained at the end of the intervention period to pre-intervention values using a repeated measures ANOVA with site included as a covariate (or a site-stratified Wilcoxon signed-rank test, if the data are skewed or heavy-tailed). To determine whether the intervention effect (if any) is modified by nurses' perceptions of their work, we will check the interaction between treatment and nurse ratings of professional status and adequacy of staffing.

We will use an intent-to-treat approach in which patients are analyzed according to the period in which they were enrolled. In our analysis of three- and six-month cessation rates, those who are lost to follow-up will be considered failures (*i.e*., still smoking). Using this approach, however, some bias may be introduced on account of informative censoring (even if the pattern of missingness is evenly distributed across baseline and intervention periods). For this reason, we will also conduct analyses to examine the patterns of missingness, and will perform sensitivity analyses to compare intervention effects under a range of assumptions regarding the mechanism of missingness [85,86]. All tests will be two-sided and will use a p-value of 0.05 for statistical significance. To fit the hierarchical models, we will use SAS (PROC GLIMMIX).

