**Outcomes:**

The primary endpoint is seven-day point prevalence abstinence at six months following hospital admission and prolonged abstinence after a one-month grace period. To compare abstinence rates during the intervention and baseline periods, we will use random effects logistic regression models, which take the clustered nature of the data within nurses and hospitals into account. We will assess attitudes of staff nurses toward cessation counseling by questionnaire and will identify barriers and facilitators to implementation by using clinician focus groups. To determine the short-term incremental cost per quitter from the perspective of the VA health care system, we will calculate cessation-related costs incurred during the initial hospitalization and six-month follow-up period.

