### Study aims

The proposed study will test an implementation intervention to increase quit rates in hospitalized smokers in noncritical care settings by facilitating staff nurses' delivery of recommended smoking cessation services and reducing patient barriers to participation in cessation counseling. Of all the members of the inpatient team, VA staff nurses (including registered nurses (RNs) and licensed practical nurses (LPNs)) are best positioned to deliver a brief smoking cessation intervention because of their ready access to patients and education in patient education and counseling. Several controlled trials have demonstrated that nurse-delivered counseling can increase quit rates in hospitalized patients [19-22]. Although most of these trials have employed high-intensity interventions [11], low intensity counseling by staff nurses can also yield favorable results [23].

Thus, the primary aim of this practical clinical trial is to:

1. Determine the effect of a nurse-initiated intervention, which couples low intensity inpatient counseling with sustained proactive telephone counseling, on smoking abstinence in hospitalized patients.

Hypothesis 1a: Smoking cessation rates at three and six month follow-up, as measured by seven-day point prevalence abstinence (PPA) will be greater for intervention patients than usual care patients.

Hypothesis 1b: Intervention patients will be more likely to receive prescriptions for recommended pharmacotherapy for smoking cessation and referral to telephone counseling, compared to usual care patients.

To gain insight into mechanisms promoting the adoption of recommended practices by nurses and to determine the relative economic value of the intervention, key secondary aims are to:

1. Determine the impact of the intervention on nurses' attitudes toward and self-efficacy for providing smoking cessation counseling.

Hypothesis 2: Nurses attitudes toward cessation counseling and self-efficacy in providing such counseling will increase after being exposed to the intervention.

2. Identify barriers and facilitators to implementation of smoking cessation guidelines in VA hospitals and learn how to tailor the intervention to specific sites.

3. Determine the short-term cost-effectiveness of this implementation intervention.

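### The primary clinical endpoint is defined in two conflicting ways, and only the component they share, six-month seven-day abstinence, is powered

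*Protocol article*

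**What the plan says.** **Abstract, Outcomes.** "The primary endpoint is seven-day point prevalence abstinence at six months following hospital admission and prolonged abstinence after a one-month grace period". Three months is not mentioned.

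**Study aims, Hypothesis 1a.** The primary aim's clinical hypothesis concerns "Smoking cessation rates at three and six month follow-up, as measured by seven-day point prevalence abstinence (PPA"). Prolonged abstinence is not mentioned.

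**Statistical analysis.** "The primary clinical endpoint of this analysis is seven-day PPA at three and six months". Prolonged abstinence is again absent. Later in the same section: "All tests will be two-sided and will use a p-value of 0.05 for statistical significance".

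**Patient-level data.** Prolonged abstinence is introduced as something that will also be determined at each follow-up, alongside seven-day and 30-day PPA. Nothing there marks it as primary.

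**Sample size calculations.** From a 12% control rate for six-month seven-day PPA, "a study sample of 1,000 patients will have 83% power to detect a seven percentage-point difference between periods in six-month quit rates". No control rate, effect or power is given for three-month PPA or prolonged abstinence.

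**Process endpoint.** Hypothesis 1b reads "Intervention patients will be more likely to receive prescriptions for recommended pharmacotherapy for smoking cessation and referral to telephone counseling". The Statistical analysis section counts referral to telephone counseling or to other outpatient cessation counseling. The 12% planning rate in the sample size section is for cessation counseling referral in general.

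**The concern.** The abstract and the analysis section both give the primary clinical endpoint, and they disagree. They share six-month seven-day PPA but differ on the second measure: prolonged abstinence in one, three-month PPA in the other. This is more than detail left for a later document, because an analysis plan that follows one passage contradicts the other.

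The unsettled matter is what decides the trial. If the two measures in a version are alternatives, each tested at 0.05, the error rate for the primary claim is above 5%. If both must succeed, the power for the primary claim is below 83%. If the choice between versions is made once results are known, the claim is not prespecified at all. In an unrandomized before-after study, a fixed primary endpoint is one of the main protections against selective reporting.

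**Working it through.** **1. The definitions side by side**

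| Place | Six-month PPA | Three-month PPA | Prolonged abstinence |
|---|---|---|---|
| Abstract, Outcomes | primary | not named | primary |
| Hypothesis 1a | in the hypothesis | in the hypothesis | not named |
| Statistical analysis | primary | primary | not named |
| Patient-level data | measured | measured | also measured |
| Sample size calculations | powered | not powered | not powered |

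There are two definitions with two measures each. The sample size section defines no primary endpoint; it powers the shared one.

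**2. Reproducing the stated 83%**

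Inputs from the sample size section: p1 = 0.12, p2 = 0.12 + 0.07 = 0.19, n = 500 per period, intracluster correlation (ICC) 0.01 within nurse. Two-sided alpha of 0.05 is from the analysis section. Nurse numbers are from Table 1: 42 + 72 + 60 + 52 = 226. The cluster size used by the authors is not stated, so I take m = 500/226 = 2.21 (one period) and m = 1000/226 = 4.42 (both periods) as assumptions.

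Formula, with continuity correction: power = Φ{[0.07 − 1/n − 1.96·√(2·p̄(1−p̄)/n)] / √[(p1(1−p1) + p2(1−p2))/n]}, where p̄ = 0.155. With clustering, n is replaced by n/DE, with DE = 1 + (m − 1)·0.01.

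- No clustering, n = 500: the two standard errors are 0.02289 and 0.02278. Power = Φ[(0.068 − 0.04486)/0.02278] = 84.5% (86.5% uncorrected).
- m = 2.21: DE = 1.012, n = 494.0, power 84.1% (86.1% uncorrected).
- m = 4.42: DE = 1.034, n = 483.5, power 83.2% (85.4% uncorrected).

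The 83% is sound for six-month PPA. Patients lost to follow-up count as smokers, so n is not reduced.

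**3. Two primary tests, either may succeed**

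False-positive rate = 1 − P(|Z1| < 1.96 and |Z2| < 1.96), with Z1 and Z2 standard bivariate normal with correlation ρ. The protocol gives no ρ, so it is varied. The same calculation serves both versions.

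| ρ | False-positive rate |
|---|---|
| 0 | 9.75% |
| 0.5 | 9.1% |
| 0.7 | 8.3% |
| 0.9 | 7.0% |

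**4. Two primary tests, both must succeed**

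Joint power = P(Z1 < 0.954 and Z2 < 0.954), where 0.954 = Φ⁻¹(0.83). This assumes 83% power for each measure.

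| ρ | Joint power |
|---|---|
| 0 | 68.9% |
| 0.5 | 72.9% |
| 0.7 | 75.2% |
| 0.9 | 78.5% |

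The 83% for the second measure is not supported by the protocol. For prolonged abstinence, assumed control rates of 4% to 12% and differences of 3 to 7 points give single-test power from 28% (12% against 15%) to 99% (4% against 11%), with 500 per period, no clustering and no continuity correction. Joint power cannot exceed the lower of the two single-test powers, so step 4 is illustrative.

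**5. If two primaries were kept with alpha split equally**

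At 0.025 each, 2.241 replaces 1.96 in step 2. Power for six-month PPA becomes 76.2% (m = 2.21) or 75.2% (m = 4.42), against 84.1% and 83.2% at 0.05.

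**The case against.** The best defence is that six-month seven-day PPA appears in every version, is the measure powered, and matches the six-month quit rates in the cost-effectiveness ratio. The 83% is therefore valid for the component that matters most. That stands: the sample size is not wrong, and the remedy is easy. It does not show which measure, if any, shares primary status with six-month PPA.

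A second defence is that multiplicity rules are commonly left to an analysis plan, and that a blanket 0.05 statement is ordinary. This also stands: the missing success rule would not be a finding by itself. The finding is the contradiction, which a later plan cannot resolve without overriding one of the passages.

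Some stronger readings are tempting but not supported:

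- A reader might infer three definitions, or three primary abstinence tests with a correspondingly larger error rate. Each definition names two measures. Three arise only by merging two conflicting passages, so the two-test figures are the ones that describe a stated plan.
- A reader might infer that three-month PPA is the easiest measure to win, because it falls near the nominal end of a telephone course of up to three months. The protocol gives no three-month rates, the call schedule is flexible, and relapsed smokers may have a further course.
- A reader might ask for an anchor date. The abstract gives one, hospital admission, and no section gives a conflicting one.
- A reader might fold the process endpoints into this conflict. They are labelled separately and have their own power figures (81% and 83%). Only the narrower referral wording of Hypothesis 1b is out of line.

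**Conclusion.** The point holds as a contradiction between two definitions of the primary clinical endpoint, with power given only for the measure they share. It should be resolved before outcomes are analysed, because it concerns what counts as success.

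The size depends on how the text is read. Under either version, success on either measure gives a false-positive rate of about 7% to 9%, and a requirement for both gives joint power of about 73% to 78.5%. Both ranges assume a correlation of 0.5 to 0.9 between the tests, and the second also assumes 83% power for each measure. Neither assumption comes from the protocol. The nominal 5% and the stated 83% hold together only if six-month seven-day PPA alone decides the trial.

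The referral mismatch in Hypothesis 1b is a separate, minor wording point, and the main conclusion does not depend on it.

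**What to change.** In the abstract, Hypothesis 1a and the Statistical analysis section, name seven-day PPA at six months as the sole primary clinical endpoint. List three-month PPA and prolonged abstinence as secondary in each place. This changes wording only: no patients, data collection or sample size are affected, and the stated 83% at two-sided 0.05 then applies to the primary claim as written.

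If two primary measures are truly intended, choose one pair and use it everywhere. State whether either or both must succeed and how alpha is shared, and give a control rate, effect and power for the second measure. That also resolves the contradiction, but the 83% could no longer be quoted as the power for the primary claim without recalculation.

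As a minor separate edit, word the referral part of Hypothesis 1b as the analysis section does (telephone or other outpatient cessation counseling), which fits the 12% planning rate.

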Patients who express an interest in quitting will be shown a 12-minute educational program on closed-circuit television, produced specifically for hospitalized VA smokers, and will receive a self-help guide to smoking cessation ('Clearing the Air: Quit Smoking Today', developed by the National Cancer Institute) [51]. Similar educational aids have been effectively used as an adjunct in counseling hospitalized smokers [7,20], and can reduce the time required for bedside counseling.

Nurses will be trained to electronically refer those patients who are willing and ready to make a quit attempt for proactive telephone counseling using a computerized referral process, based on evidence that VA patients who receive such counseling are more likely to quit [47]. Within 48 to 72 hours of discharge, a quit line counselor will call to confirm the patient's interest in quitting, congratulate the patient on his/her decision to stop smoking, and provide encouragement to reinforce self-efficacy. For those patients who are ambivalent about quitting, the counselor will focus on increasing motivation to quit. For those patients who remain committed to quitting, the counselor will focus on relapse prevention [52].

Follow-up calls will be made using a relapse-sensitive schedule (rather than at equal intervals) [13], with flexibility to accommodate the patient's needs (up to seven calls over three months) [47,53]. Telephone counselors will document the initial and follow-up contacts in CPRS using progress note templates for smoking cessation [54]. A final report summarizing events pertinent to the quit attempt will also be entered into CPRS shortly after the final counseling session (and will be mailed to the patient's non-VA primary care clinician, if applicable). Enabling bi-directional communication with primary care will integrate the telephone counseling into the patient's ongoing care [55,56]. We will also offer one additional course of quit line counseling for relapsed smokers (*i.e*., those who fail in their initial quit attempt).

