### Patient-level data

After obtaining informed consent, the RA will perform a structured interview in current smokers to obtain more detailed information on smoking history (pack-years, number of quit attempts more than one day), other tobacco use (*e.g*., spit tobacco), alcohol use, overall health status, smoking-related medical comorbidities, readiness to quit smoking [23], level of tobacco addiction [71], perceived likelihood of staying off cigarettes after hospital discharge [72], and social support for quitting [6].

Just prior to discharge, the RA will ask eligible smokers whether they abstained from cigarettes during hospitalization, and whether or not the hospital staff had performed recommended smoking cessation counseling during the hospital stay. Patients will also be asked to specify whether they had received these services from their nurse, physician, or other clinician (*e.g*., respiratory therapist) [73]. Patient recall of advice to quit smoking has been shown to be reasonably accurate in assessing performance of guideline-recommended actions in clinical practice (sensitivity 92%, specificity 82% for advice to quit) [74].

At three- and six-month follow-up, research interviewers will contact patients by telephone about their smoking over seven days and 30 days prior to the interview (seven-day and 30-day, PPA), any quit attempts (>24 hours) since hospital discharge, and stage of change. At each follow-up, we will also determine prolonged abstinence (after a one-month grace period). All follow-up interviewers will be blinded to treatment assignment. Patients who report abstinence at six-month follow-up will be mailed a collection kit for salivary cotinine determination (with a follow-up telephone reminder to return the sample). A cutoff of 20 ng/ml will be used to determine abstinence, as this threshold is associated with high sensitivity and specificity (>90%) [75]. To calculate the biochemically confirmed six-month quit rate, we will adjust the seven-day PPA for the results of the cotinine analysis.

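### The primary clinical endpoint is defined in two conflicting ways, and the 5% error rate and 83% power hold together only for a single test of six-month abstinence

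*Protocol article*

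**What the plan says.** The protocol article defines the primary clinical endpoint in three places, and they do not agree.

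- **Abstract, Outcomes:** "The primary endpoint is seven-day point prevalence abstinence at six months following hospital admission and prolonged abstinence after a one-month grace period".
- **Study aims, Hypothesis 1a:** "Smoking cessation rates at three and six month follow-up, as measured by seven-day point prevalence abstinence (PPA) will be greater for intervention patients".
- **Statistical analysis:** "The primary clinical endpoint of this analysis is seven-day PPA at three and six months".

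Under Patient-level data, prolonged abstinence is collected but not ranked: "At each follow-up, we will also determine prolonged abstinence (after a one-month grace period". The same section sends cotinine kits only to patients who report abstinence at six months.

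Sample size calculations assumes a 12% control quit rate for six-month seven-day PPA and states that "a study sample of 1,000 patients will have 83% power to detect a seven percentage-point difference between periods in six-month quit rates". It gives no rate or power for three-month PPA or prolonged abstinence. The last paragraph of Statistical analysis sets two-sided 0.05 for all tests.

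**The concern.** Prolonged abstinence is primary in the Abstract but is not named in Hypothesis 1a or in the definition under Statistical analysis. Three-month PPA is primary in those two places but is not named as primary in the Abstract. This is a contradiction in the current text. An analysis plan could follow one version only by departing from the other.

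The primary endpoint decides whether the trial succeeded. This is an unrandomized before-after study, so any freedom to settle that definition after the data are seen weakens the result further. The planning figures also belong to one outcome only. If the primary claim rests on two, the 5% error rate and the 83% power cannot both be carried over to it.

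**Working it through.** **1. The definitions side by side**

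| Measure | Abstract | Hypothesis 1a | Statistical analysis | Planning rate and power given |
|---|---|---|---|---|
| Six-month PPA | primary | yes | primary | 12%, 83% |
| Three-month PPA | not named | yes | primary | none |
| Prolonged abstinence | primary | not named | not named | none |

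Only six-month PPA appears in every column.

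**2. Reproducing the stated power for one test of six-month PPA**

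Inputs from Sample size calculations: 500 per period, 12% against 12 + 7 = 19%, intracluster correlation (ICC) 0.01. Two-sided 0.05 is from Statistical analysis.

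- Mean rate: (0.12 + 0.19)/2 = 0.155.
- Null standard error: √(2 × 0.155 × 0.845/500) = 0.02289.
- Alternative standard error: √((0.12 × 0.88 + 0.19 × 0.81)/500) = 0.02278.
- Power: Φ[(0.07 − 1.96 × 0.02289)/0.02278] = Φ(1.103) = 86.5% before clustering.

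The number of patients per nurse (m) is not stated, so it is assumed from Table 1. There are 42 + 72 + 60 + 52 = 226 nurses, and 1000/226 = 4.42. The design effect is 1 + (4.42 − 1) × 0.01 = 1.034, which leaves an effective 500/1.034 ≈ 484 per period. Power is then 85.4%, or 83.2% with a continuity correction. With registered nurses only (about 151, m ≈ 6.6) the figures are 84.6% and 82.4%. The stated 83% is therefore reproduced to within about two points for a single test.

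**3. Two primary endpoints, each tested at two-sided 0.05**

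The documents give no correlation between endpoints and no effect for the second one. Two assumptions are made: the test statistics are jointly normal with correlation ρ of 0.5 to 0.8, and each endpoint alone has 83% power (mean 1.960 + 0.954 = 2.914). Results are from simulation, except that power if either suffices is 2 × 0.83 minus the joint power.

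| | ρ = 0.5 | ρ = 0.8 |
|---|---|---|
| Either suffices: type I error | 9.1% | 7.8% |
| Either suffices: power | 1.66 − 0.729 = 93.1% | 1.66 − 0.766 = 89.4% |
| Both required: type I error | at most 5% | at most 5% |
| Both required: power | 72.9% | 76.6% |

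For reference, independent tests give 1 − 0.95² = 9.75% error if either suffices and 0.83² = 68.9% power if both are required.

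**4. Sensitivity**

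If single-test power is taken as 85.4% (m = 4.42, no continuity correction), both-required power is 76.3 to 79.6% over the same correlations. At 86.5% it is 78.0 to 81.1%. Whatever the correlation, both-required power cannot exceed the power of the weaker endpoint.

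**The case against.** The strongest reply has four parts.

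- **The body agrees with itself.** Hypothesis 1a matches Statistical analysis, and the outlier is one sentence in the Abstract. That is true and makes the repair easy. But the body version also names two time points, and only one is powered, so deleting the Abstract wording would not settle the matter.
- **The rule for combining endpoints may be in an analysis plan that is not shown.** This stands. The absence of a rule is not the point here. The point is that the definitions conflict and the planning figures fit only their common element. Every version joins its measures with the word and, so the either-suffices reading is not stated anywhere. It is one of two possible readings.
- **The sizes rest on assumptions.** This also stands. The correlation and the second endpoint's 83% power are assumed. A better-powered second endpoint would bring joint power closer to 83%.
- **Three-month PPA is not shown to be a bad endpoint.** A reader might infer that it is measured on treatment, because counseling allows "up to seven calls over three months" after discharge while the Abstract counts six months from admission. The documents support this only in part. The three-month interview may overlap counseling, but Self-management support also offers a further course after relapse, so counseling could run on towards six months too. What is clear is narrower: three-month abstinence is self-report only. Even there, the contrast should not be overdrawn, because Statistical analysis does not say that the six-month primary is the cotinine-adjusted rate.

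**Conclusion.** The contradiction is real and must be resolved. The 5% error rate and the 83% power are supported together only for a single test of six-month PPA. With two primary endpoints, one of the two figures gives way: about 7.8 to 9.1% error if either suffices, or about 73 to 77% power if both are required. These sizes assume a correlation of 0.5 to 0.8 and 83% power for each endpoint.

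Two stronger readings should be set aside. A reader might infer that the primary claim has neither the 5% error rate nor the 83% power. No single reading fails both ways: where error is inflated, power is above 83% (about 89 to 93%), and where power falls, error is controlled. A reader might also count three co-primary abstinence outcomes and quote larger figures. No section lists three, and that count pools two incompatible definitions. The separately labelled endpoints ("The primary process of care endpoints are referral of patients to telephone counseling (or other outpatient cessation counseling) and prescription of recommended pharmacotherapy") belong to Hypothesis 1b and are not part of this calculation.

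**What to change.** In the Abstract (Outcomes), Hypothesis 1a and Statistical analysis, name seven-day PPA at six months as the single primary clinical endpoint. List three-month PPA and prolonged abstinence as secondary, with no part in the primary claim, and note that three-month PPA is self-report only. The sample size, the data collection and the 83% figure then stand unchanged.

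The cost is wording. The downside is that a positive three-month or prolonged-abstinence result alone can no longer be called a primary success.

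Keeping two primaries is possible but dearer. It needs a stated decision rule and new power figures. For example, splitting alpha to 0.025 each lowers per-test power from 83% to about 75%. Regaining 83% would need ((2.241 + 0.954)/(1.960 + 0.954))² ≈ 1.20 times the sample, again assuming equal power for the second endpoint.
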